### Clinical and instrumental assessments

Assessments will be performed at recruitment (T0), after the 4 weeks (T1) and after 12 weeks (T2).

Clinical evaluation (planned at T0, T1 and T2) will be supported by the clinical scales recommended by the Italian Society of Physical and Rehabilitation Medicine (41) and includes the CRS-R and the LCF, the Disability Rating Scale (DRS) and the Functional Independence Measures (FIM). Dysphagia will be assessed by the Mann Assessment of Swallowing Ability (MASA) Scale and the FOIS. At T2, the Glasgow Outcome Scale-Extended (GOSE-E) (42) will be performed.

The instrumental evaluations will include the Fiberoptic Endoscopic Evaluation of Swallowing (FEES) (43) integrating the compilation of the Pooling score.

To identify possible confounding factors such as Epileptic status and Intensive Care Unit-Acquired Weakness may interfere with the swallowing function, other data will be recorded from instrumental exams included in the routinary clinical practice (standard electroencephalography-EEG and Electroneuro/myography-ENG/EMG) (44).

Finally, the decannulation achievement and its timing and the infection rate will be recorded.

For the purposes of this study, infections will be recorded as clinical events requiring initiation or escalation of systemic antibiotic therapy supported by clinical signs and, when available, microbiological sampling. Pneumonia will be recorded when respiratory infection is the primary suspected source and is supported by: (i) new or progressive and persistent pulmonary infiltrate/consolidation on chest imaging; (ii) at least two of the following: fever or hypothermia, leukocytosis/leukopenia, purulent respiratory secretions or increased suctioning needs, worsening gas exchange/increased oxygen requirement, or new/worsening cough/dyspnea/tachypnea; with (iii) microbiological support when available (e.g., positive culture from respiratory secretions).

All evaluations will be performed by professionals blinded to the treatment/control arm. Moreover, patients enrolled in the study, given their state of unconsciousness and behavioral/cognitive confusion, may be considered blinded for the purpose of the received AA treatment.

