### Randomization, allocation concealment and blinding

After enrollment, patients will be allocated to one of two groups by computerized randomization and stratified by MASA scale, with an allocation ratio of 1:1, and assigned to either the control or intervention arm. Allocation concealment will be ensured via sequentially numbered, opaque, sealed envelopes prepared by an independent statistician (see Figure 2). The study is designed as double-blind: all clinical and instrumental assessments will be performed by professionals blinded to the treatment arm, and patients are considered blinded either because they present a DoC or due to severe cognitive impairment with short-term memory deficits, which prevent them from being aware of or recalling the treatment received. Due to the nature of the acupuncture intervention, blinding of the acupuncturist is not feasible and represents a potential source of performance bias. To minimize its impact, several mitigation strategies were implemented *a priori*. Acupuncturists will not be involved in outcome assessment, rehabilitation planning, or data analysis. The intervention will be delivered according to a standardized protocol, including fixed session duration, predefined acupuncture points, and uniform treatment setting. Outcome assessors and the rehabilitation team will remain blinded to group allocation throughout the study. Any accidental unblinding will be documented.

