### Statistical analysis

At present, we have designed a pilot study with the purpose of providing preliminary data necessary to calculate the appropriate sample size for a subsequent randomized controlled trial (RCT). The main study will be a 2-arm, randomized, controlled trial for which a medium effect size was conservatively hypothesized. According to the stepped rules of thumb proposed to estimate the size of the pilot based on Cohen’s d effect size (55), for an 80% power main trial, the pilot sample size should be 10 per arm, and the subsequent main trial will require somewhere between 34 and 176 participants per arm. The sample size of 10 participants per arm will be increased to 12 participants per arm to account for potential dropouts. This sample size was determined exclusively since methodological recommendations available in the literature. The data obtained from this pilot study will be used to estimate the effect size and variability, which will inform the power analysis and the determination of the required sample size for the definitive RCT. Analyses will be conducted using SPSS version 28 software (SPSS, SPSS Inc., Chicago, United States). The normality of the distribution of continuous variables will be checked using the Shapiro–Wilk test. If the variables violate the assumption of normality, they will be presented through their median value and interquartile range, otherwise through mean and standard deviation. Categorical variables will be represented through absolute frequencies and percentages. Baseline characteristics will be compared between treatment and control groups using independent *t*-tests or Mann–Whitney U tests for continuous variables, depending on data distribution, and chi-square or Fisher’s exact tests for categorical variables. The primary outcome (improvement in dysphagia) will be assessed by comparing MASA scores and “Pooling score” between groups at T1 using ANCOVA models (adjusting for baseline values) or non-parametric alternatives, if assumptions are not met. Maintenance of the effect at T2 will be evaluated using linear mixed models with random intercepts, including group, time (baseline, T1, T2), and their interaction as fixed effects; if model assumptions are violated, change scores between T1 and T2 will be calculated and compared between groups using independent *t*-tests or Mann–Whitney U tests. Secondary outcomes will be analyzed as follows: decannulation rates at T1 and T2 will be compared between groups using chi-square or Fisher’s exact tests, while decannulation times will be compared using independent *t*-tests or Mann–Whitney U tests and Kaplan–Meier survival analysis. Infection rates at T1 and T2 will be compared between groups using chi-square or Fisher’s exact tests. Functional autonomy at T2, measured by the GOS-E, will be compared between groups using independent *t*-tests if normality assumptions are met, or Mann–Whitney U tests otherwise. A *p*-value <0.05 will be considered significant in all analyses. The primary analysis will follow the intention-to-treat (ITT) principle. Sensitivity analysis will be performed to assess the robustness of the findings, including per-protocol analysis restricted to patients who completed the assigned intervention.

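### Randomisation is stratified by MASA, but the GOS-E, decannulation and infection comparisons are fixed as unadjusted tests that ignore the stratum (minor)

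*Protocol article*

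**What the plan says.** The Protocol article, under Randomization, allocation concealment and blinding, has patients "allocated to one of two groups by computerized randomization and stratified by MASA scale, with an allocation ratio of 1:1". It gives neither the number of MASA strata nor their cut-points.

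Under Statistical analysis, each outcome has a named method:

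- **MASA and Pooling score at T1:** compared "using ANCOVA models (adjusting for baseline values) or non-parametric alternatives, if assumptions are not met".
- **MASA and Pooling score at T2:** a random-intercept mixed model in which T0 is one of the time levels.
- **GOS-E:** "Functional autonomy at T2, measured by the GOS-E, will be compared between groups using independent" t-tests, or Mann–Whitney tests if normality fails.
- **Decannulation rate and infection rate at T1 and T2:** chi-square or Fisher tests.
- **Decannulation time:** t-tests or Mann–Whitney tests, plus Kaplan–Meier analysis.

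The last three entries contain no stratum and no covariate. GOS-E has no baseline of its own: "At T2, the Glasgow Outcome Scale-Extended (GOSE-E) (42) will be performed". MASA, FOIS, CRS-R, LCF, DRS and FIM are all recorded at T0 (Clinical and instrumental assessments). A significance threshold of 0.05 applies to every analysis, and the trial is described as a pilot that supplies effect-size and variability estimates for a later RCT.

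**The concern.** Stratified randomisation balances MASA categories between the arms. If MASA predicts the outcome, this reduces the true sampling variance of the treatment difference. An unadjusted test still estimates its standard error from the full between-patient variance, including the part due to the stratum. The standard error is then too large, the interval too wide and the p-value conservative, so the precision gained by design is not used.

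Stratifying by MASA makes most sense if MASA is thought to be prognostic. The Introduction itself names persistent dysphagia as a major obstacle to decannulation. The protocol names the unadjusted tests outright, so this is a stated choice and not a detail left open. At stake is the precision of the secondary comparisons, and a variability estimate for these outcomes that still contains stratum variance.

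**Working it through.** **The plan's own figure.** The main-trial range comes with the statement that "the pilot sample size should be 10 per arm, and the subsequent main trial will require somewhere between 34 and 176 participants per arm", for which "a medium effect size was conservatively hypothesized". Taking medium as d = 0.3 to 0.7 (assumed), with two-sided alpha 0.05 (sidedness assumed) and 80% power, the exact t-test gives 175.4 → 176 and 33.02 → 34 per arm. The range reproduces. The rise from 10 to 12 per arm implies a loss of 1 − 10/12 = 16.7%.

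**Inputs for the check.** From the documents: 12 per arm, 1:1 allocation, stratification by MASA, alpha 0.05. Assumed: two strata of equal size, balance within each stratum, a normally distributed outcome, d = 0.5, and a baseline–outcome correlation r from 0 to 0.7.

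**Continuous-type outcome such as GOS-E.** In 40,000 simulated trials per row, y = r·x + √(1 − r²)·e + d·group, with strata formed by a median split of x.

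| r | Type I error, stratum ignored | Type I error, stratum in model | Power, ignored | Power, in model | Mean 95% CI width, ignored / in model (d = 0) |
|---|---|---|---|---|---|
| 0 | 5.1% | 5.1% | 21.9% | 21.7% | 1.674 / 1.677 = 1.00 |
| 0.3 | 4.4% | 5.1% | 20.7% | 22.4% | 1.676 / 1.629 = 1.03 |
| 0.5 | 3.5% | 5.2% | 19.3% | 24.5% | 1.679 / 1.541 = 1.09 |
| 0.7 | 1.9% | 5.0% | 17.5% | 28.8% | 1.686 / 1.399 = 1.21 |

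The mechanism shows at r = 0.5. The unadjusted test reports a mean standard error of 0.405, while the estimate actually varies with standard deviation 0.378, and 0.405/0.378 = 1.07. With the stratum in the model the reported value is 0.370.

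**Where adjustment stops paying.** In closed form, without using the stratified allocation, one continuous covariate changes the interval width by the factor √(1 − r²) × √(21/20) × t(21)/t(22) = 1.0275 × √(1 − r²). This equals 1 when r² = 1 − 1/1.0275² = 0.053, so r ≈ 0.23. Power at d = 0.5 is 21.6% unadjusted. Adjusted, it is 20.7%, 21.4%, 22.3%, 26.1% and 35.9% at r = 0, 0.2, 0.3, 0.5 and 0.7. Below about r = 0.25, covariate adjustment therefore gains nothing and costs slightly.

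**Binary outcomes (decannulation, infection).** Two strata of six per arm, common odds ratio 4; the control risks are assumed.

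| Control risk by stratum | Fisher | Chi-square | CMH |
|---|---|---|---|
| 0.5 / 0.5 | 20.9% | 35.8% | 35.8% |
| 0.3 / 0.7 | 14.2% | 27.4% | 28.9% |
| 0.2 / 0.8 | 7.0% | 17.1% | 22.5% |

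The gain due to stratifying is CMH minus chi-square: 0, 1.5 and 5.4 points. Much of the gap to Fisher is discreteness, not the stratum. With odds ratio 1, the rejection rates for Fisher, chi-square and CMH are 2.2%, 6.4% and 6.4% in the first row, 1.4%, 4.4% and 5.1% in the second, and 0.4%, 2.0% and 3.7% in the third.

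**The case against.** The strongest reply is that little is lost. These are secondary outcomes of a pilot, power at d = 0.5 stays below 40% in every scenario, and the error is conservative, so no false positives are added. The correlation is unknown. Eligibility is narrowed to FOIS = 1 and LCF ≤ 4 with UWS excluded, and the Discussion concedes that MASA can be less reliable in non-communicative patients. Both may weaken MASA as a predictor. All of this stands and keeps the point minor. It does not remove it: the plan still tests these outcomes at 0.05 and means to carry variability estimates forward.

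Four stronger readings are tempting, and the documents do not support them.

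- **The Pooling score analysis ignores baseline.** It does not. Its T1 ANCOVA adjusts for baseline values and its mixed model contains the T0 measurement. At most, the text does not say whether the MASA stratum enters as well.
- **The non-parametric fallback for the primary ANCOVA drops the baseline.** That would follow only from a test such as Mann–Whitney. The article names none, and the choice may sit in an analysis plan that is not shown.
- **The loss is large.** A reader might compute 12/(1 − r²) = 13.2, 16.0 and 23.5 effective patients per arm at r = 0.3, 0.5 and 0.7, or a true test level of 2.4% at r = 0.5 (standard error too large by 1/√0.75 = 1.155). The first ignores the lost degree of freedom and residual imbalance. At r = 0.3 the closed-form width ratio is 0.98, so the equivalent is 12/0.98² = 12.5 per arm. The second assumes complete balance on the continuous score, whereas two strata give 3.5%.
- **Every collected baseline should be used.** With 24 patients, only the stratum or one covariate is workable.

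**Conclusion.** The point holds for GOS-E, decannulation rate and time, and infections. The design stratifies by MASA, while the stated tests for these outcomes ignore it. If MASA is prognostic, the tests run below their nominal level and the intervals are about 3%, 9% and 21% wider than a stratum-adjusted analysis would give at r = 0.3, 0.5 and 0.7. The power forgone at d = 0.5 is 1.7, 5.2 and 11.3 points respectively (22.4 − 20.7, 24.5 − 19.3, 28.8 − 17.5). For the binary outcomes, the gain from stratifying ranges from nothing to about 5 points under the assumed risks.

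These sizes rest on two equal strata, normal outcomes and correlations that the documents do not give. If MASA is not prognostic, nothing is lost by the present plan. The primary MASA and Pooling score analyses are not affected. Severity is minor.

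**What to change.** In the Statistical analysis section, or in the analysis plan before unblinding:

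1. Analyse GOS-E at T2 with one pre-specified baseline term, either baseline MASA or the MASA stratum. Use a van Elteren test stratified by MASA if normality fails.
2. Compare decannulation and infection rates with a MASA-stratified test, CMH or exact. State which in advance: the simulated CMH level reached 6.4% when there was no stratum effect, while an exact test is likely to be more conservative.
3. Compare decannulation time with a log-rank test stratified by MASA, alongside the planned Kaplan–Meier curves.

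The cost is a few sentences and one degree of freedom, and MASA at T0 is already collected. The downsides are a slight loss if MASA turns out to be weakly prognostic, and sparse cells if more than two strata are used with 12 per arm. No change is needed to the Pooling score ANCOVA on this account.

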
### Data collection and management

Data will be collected through electronic case report forms (eCRFs) using the REDCap platform. Data entry will include built-in logic and range checks to ensure accuracy. All identifying information will be pseudonymized. Access to the database will be password-protected and restricted to authorized personnel only. Data will be stored on secure servers for 7 years after trial completion before anonymization.

### Data monitoring and quality assurance

Monitoring will be conducted by an independent study monitor from the research coordination office of the IRCCS. Source data verification will be performed on at least 10% of cases. Any protocol deviation will be documented and assessed for impact on study integrity.

## Discussion

The rehabilitation of dysphagia in patients surviving a sABI presents a significant challenge, particularly when initiated in the early phase in which patient cooperation is minimal or absent. In such cases, speech-language rehabilitation techniques requiring active patient participation are not feasible. Instead, passive or neuromodulation-based approaches must be considered. Within this context, acupuncture and auriculotherapy emerge as promising treatment options since these therapies do not rely on patient cooperation. The main purpose of this study is to determine whether acupuncture and auriculotherapy can serve as an appropriate and effective treatment for rehabilitating dysphagia in non-communicative patients surviving a sABI.

The present study protocol has been carefully designed to consider not only the individual characteristics of dysphagia, the patient population, and the proposed intervention, but also the dynamic interactions among these three factors. An accurate assessment of swallowing function represents a critical step for monitoring the primary outcome namely the progression of dysphagia throughout the rehabilitation process. For this purpose, in addition to FOIS offering a crude description of dysphagia, the MASA, a bedside clinical scale for swallowing consisting of 26 items that can be easily administered by speech therapists, was chosen. This scale has demonstrated good psychometric properties in brain-injured patients with cognitive impairment (53) and has been used in tracheostomized patients (56). As is often the case with clinical scales, the reliability of the MASA can be reduced in non-communicative patients because some items—such as auditory comprehension, expressive communication, alertness, cooperation, command following, apraxia, articulation, oral preparation and transit, and respiratory-swallow coordination—can be challenging to administer. To mitigate this limitation, an instrumental evaluation by FEES to detect any changes—including subclinical ones—in swallowing function is included in this study. This dynamic endoscopic technique primarily evaluates the pharyngeal phase of swallowing—excluding the whiteout period—while also providing indirect information about the oral and esophageal phases. Furthermore, FEES allows for the targeted assessment of laryngeal sphincter function, sensory responsiveness, and the presence of pharyngeal residue. Its minimally invasive nature and feasibility for bedside application make it particularly suitable for patients in unstable clinical conditions (57). Given the complexity of these cases, which often involve reduced responsiveness and impaired postural control, FEES is strongly recommended both to guide the initiation of oral feeding rehabilitation programs (58, 59) and to support decisions regarding decannulation The Pooling Score, a clinical endoscopic evaluation will be used to assess the severity of swallowing disorders, considering excess residue in the pharynx and larynx (43). This score ranges from a minimum of 4 to a maximum of 11 and is calculated by summing the scores assigned to: Bolus location, Amount of residue, Ability to control residue/bolus pooling, assessed based on coughing, throat clearing (raclage), and the number of dry voluntary or reflex swallowing attempts (<2, 2–5, >5).

In addition to the characteristics of dysphagia itself, several peculiarities of sABI patients—such as functional status, neck posture in a seated position, muscle tone, level of consciousness, and cognitive function—must be carefully considered, as they can significantly influence its severity. For this reason, a precise multidisciplinary assessment was incorporated into the selection of evaluation scales (DRS, FIM, CRS-R, LCF). The CRS-r (60, 61) is the main current clinical assessment tool for the behavioral diagnosis of DOC, while the LCF is widely used in monitoring the progression of cognitive recovery, with lower scores (LCF 1–3) for levels of impaired consciousness, and progressively higher scores for levels of increased cognition. To support and complement the clinical evaluation, some instrumental examinations routinely practiced in the in-patient ward were included in the study. EEG, EMG, and MEP will be performed to objectively assess potential neurological deficits or potential confounders factors, such as epileptic status, severe hyposthenia involving trunk muscles, severe critical illness neuromyopathy. Additionally, the inclusion criteria were selected based on scientific evidence and the expected clinical impact. For instance, patients in an UWS were excluded considering recent findings indicating the absence of the oral phase of swallowing in this population (16). Also, particular attention was given to minimizing heterogeneity within the study population by including only patients with a vascular etiology.

For what concerns the intervention modalities, the protocol, including the duration and frequency of treatment, was developed following a thorough review of the literature on the use of somatic and auricular acupuncture in the rehabilitation of dysphagia in patients with central neurological damage. Acupuncture, a key component of TCM, involves the insertion of fine needles with manual or electrical stimulation (62) to restore qi balance along meridians (63). Literature suggests its effectiveness in managing neurological symptoms such as spasticity and pain (64) and some randomized controlled trials reported benefits for post-stroke dysphagia (65, 66). Although, a Cochrane review found insufficient evidence due to high study heterogeneity (32), acupuncture has been recently recommended with moderate evidence by the European Stroke Organization and the European Society for Swallowing Disorders for post-stroke dysphagia treatment (30).

Auriculotherapy involves stimulation of specific points on the auricular pavilion, considered a major microsystem of the body (67). From a Western medical perspective, its effects are understood through neurophysiological and reflexogenic mechanisms (67), as the ear receives extensive innervation from four mixed cranial nerves—trigeminal, facial, glossopharyngeal, and vagus nerve—as well as from the cervical plexus (C2/C3) (68). To date, no studies have specifically investigated auriculotherapy in patients with sABI, and only limited evidence exists regarding its use in post-stroke dysphagia. Together, these points provide a multi-target approach that combines peripheral sensorimotor facilitation with central autonomic modulation. This strategy aligns with evidence suggesting that auricular stimulation may activate brainstem nuclei—such as the nucleus tractus solitarius and nucleus ambiguus—and support neuroplasticity in neurorehabilitation. The inclusion of multiple auricular points in our protocol was also motivated by practical considerations related to the clinical condition of sABI patients. Severe motor impairments, abnormal postures, spasticity, and involuntary movements often hinder access to body acupuncture points, compromising safety and feasibility. In contrast, the auricle provides a compact, easily accessible surface where stimulation can be safely administered with minimal repositioning, even in bedridden or low-responsive patients. This anatomical and logistical advantage makes auriculotherapy particularly well-suited for complex neurorehabilitation contexts. Finally, the effectiveness of somatic and auricular acupuncture will be evaluated using a treatment schedule aligned with evidence-based protocols reported in the literature (29). The persistence of treatment benefits will be assessed at follow-up (T2), conducted 2 months after the conclusion of acupuncture therapy, during which patients will continue to receive standard rehabilitation care.

